### Effect of lower sample size on statistical analysis plan

The final sample size of 108 was approximately one-third the estimated minimum required sample size of 312. As a result, one or more of our proposed mixed effects regression models (linear or logistic) may fail to converge. Nevertheless, we will attempt to fit the models as proposed in the first instance. If the model for an outcome measure fails to converge, we will approach the modelling of that outcome by removing effects from the model in the following order:Time periodmRS [18]Injury severityInjury typeSite

If the model for an outcome still fails to converge, the outcome may be modelled with separate models at each timepoint: 12 weeks or 26 weeks. In this case, time since injury and interaction between time since injury and condition (control/intervention) will be redundant. The other effects will be included in the model using a forward selection strategy to achieve the best model based on the Akaike Information Criterion (AIC). The assumptions for all statistical models will be assessed graphically using residual plots.

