## Statistical analysis plan

### Analysis principles and general considerations

All outcomes and analyses were prospectively characterised as primary or secondary.This is a superiority trial with intervention expected to yield superior outcomes, compared to control. However, all outcomes will be tested independently at the two-tailed 5% significance level. All estimates of treatment effects will be presented with 95% confidence intervalsNo formal adjustments will be undertaken to constrain the Type I error associated with planned secondary or exploratory analyses. The information provided by analyses is designed to supplement the evidence from the primary analyses; it will provide a more complete characterisation of the treatment effects.The analyses for all quantitative outcome measures will be conducted on an intention the treat (ITT) basis, i.e. all participants will be analysed in the trial phase (control or intervention) in which they were recruited, regardless of whether their treatment adhered to the trial protocol or not. The ITT strategy for this trial is based on the following principles:◦ All available outcome data are collected on all recruited participant◦ For the ITT analysis, the outcomes for each participant will be included in the data for the trial phase (control/intervention) in which the participant was recruited.◦ All available outcome data will be used in the primary analyses. The primary analyses will be reported without imputation of missing data. If the amount of missing data exceeds 10% at the primary endpoint, missing data will be imputed under the assumption that data is missing at random.◦ A sensitivity analysis including all randomised individuals will be conducted. The sensitivity analysis will consider alternative assumptions about data missing not at random (MNAR).For primary and secondary analyses, the treatment effects for the participant-level effectiveness outcomes will be adjusted for brain injury type (stroke or TBI) and severity of injury (mRS) [18] at baseline. In addition, age at recruitment, timepoint (time since injury) and time period (6-month block of time in which the participant is recruited to the step-wedge trial) will be included as fixed effects. Hospital site will be included as a random effect. Unadjusted analyses will be reported separately from these pre-specified analyses.All analyses will be conducted using the R Statistical Programming Language [32] after data collection is completed and the database is locked.

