
### Interim analysis

No interim analyses were planned for this trial. The Data and Safety Monitoring Committee (DSMC) reviewed safety and effectiveness data during the course of the trial. Due to the sequential nature of the trial (control condition precedes intervention condition at each site), there were no formal stopping conditions for effectiveness. The DSMC was guided by the Haybittle-Peto boundaries [33] in assessing safety concerns. That is, they could have recommended stopping of the trial if the number of serious adverse events (SAEs) in the intervention condition exceeded the number of SAEs in the control condition by at least 3 standard errors.

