## Changes since the commencement of the trial

### Recruitment rate

Recruitment remained below the anticipated rate throughout the trial. This was due to a number of issues including:The COVID-19 pandemic from 2020 to the trial close;Difficulty experienced in recruitment of people with TBI;A hiatus in the recruitment of participants incapable of independent consent, i.e. discontinuation of approval to gain consent by proxy from 2018 to 2020 as part of the Western Australian Guardianship and Administration Amendment (Medical Research) Act 2020 [38];Initial ethical approval for recruitment within hospital setting only—participants were often discharged before being recruited; even after approval was gained to recruit within the community, this remained problematic as many were rural residents, and recruiting remotely proved to be challenging; andLimited availability of recruiters in some hospitals at times, e.g. staffing shortages.

All assessments in this trial were designed to be undertaken remotely or in person and are validated for remote administration. Similarly, the Aboriginal Brain Injury Coordinator services were able to be undertaken via telephone and telehealth, as planned. Therefore, COVID-19 pandemic, which was declared as a global pandemic on March 23, 2020, did not affect the administration of the trial for recruited participants. Recruitment concluded on 31 July 2021, as planned. The total number of patients recruited was 108 with uneven distribution across sites and clusters. The numbers recruited by site/cluster per time period are presented in Table 7 in Appendix.

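### The non-convergence fallback removes time period before any prognostic covariate and never forces it back, so a fallback model would absorb any secular trend into the intervention effect

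*SAP article*

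**What the plan says.** The primary model (SAP article, Analysis of primary outcome) has time period as a fixed effect, and Analysis principles and general considerations defines it as the six-month block of recruitment. The fallback is in Effect of lower sample size on statistical analysis plan. With 108 participants instead of 312, the authors expect that "one or more of our proposed mixed effects regression models (linear or logistic) may fail to converge". The planned models are tried first. If one fails, terms are taken out "by removing effects from the model in the following order:Time periodmRS [18]Injury severityInjury typeSite", so time period goes first and site last. The rule applies to the model for any outcome measure, and the primary outcome is not excepted.

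If fitting still fails, separate 12- or 26-week models may be used, in which "The other effects will be included in the model using a forward selection strategy to achieve the best model based on the Akaike Information Criterion". No term is forced in at that stage.

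Two other statements matter. Interim analysis notes that "control condition precedes intervention condition at each site". Recruitment rate lists "The COVID-19 pandemic from 2020 to the trial close", a 2018–2020 gap in proxy consent, and the later approval of community recruitment. Study design adds that the recruitment window was widened from 4 to 6 weeks during Period 1.

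**The concern.** In a stepped wedge, condition is tied to calendar time by design. Baseline mRS, injury severity and injury type are prognostic covariates: losing them costs mainly precision and some protection against chance imbalance. Time period is what separates the intervention from whatever else changed over the trial. Without it, and while site stays in as a random effect, the condition coefficient is mainly a within-site before/after difference.

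A change over calendar time in quality of life, service use or the kind of patient enrolled would then be added to, or taken from, the intervention effect. Restored proxy consent and a wider recruitment route both plausibly change who is enrolled. The removal order therefore gives up the design adjuster first, and for the primary outcome it could replace the valid analysis with a confounded one that looks more precise.

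**Working it through.** **Inputs from the SAP (Sample size; Study design).** SD 25, target difference 15 points, ICC 0.08, four randomised clusters, four steps, 26-week periods, N = 108 achieved, two-sided 5%.

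**The plan's own figures.** With d = 15/25 = 0.6, 45 per group gives power 0.804 and 44 gives 0.795, so the total is 90. The cited design-effect formula with k = 4 steps, b = 1 baseline, t = 1 measurement per step and n = 13 gives

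[1 + 0.08(52 + 13 − 1)] / [1 + 0.08(26 + 13 − 1)] × 3(0.92) / [2(4 − 1/4)] = (6.12/4.04) × 0.368 = 0.5575, i.e. 0.56.

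Then 90 × 0.56 × 6 = 302.4. Divided by 24 cluster-periods this is 12.6, rounded up to 13, and 13 × 24 = 312. The stated inputs reproduce, so they are used below.

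**Assumptions.** Figure 1 and the recruitment table are not shown. Four layouts were therefore tried:
- six periods, even recruitment (4.5 per cluster-period); clusters crossing at periods 2–5 or at periods 3–6 give the same result;
- seven periods (two baseline, four steps, one extra), even recruitment;
- six periods, two of them baseline, early-sparse recruitment of 8, 10, 16, 22, 26 and 26 per period, with clusters recruiting 40:30:20:10 in order of crossover, and the same with that order reversed.

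**Formulas.** Generalised least squares on cluster-period means, with a random cluster intercept of variance 0.08 × 625 = 50 and residual variance 575/n:
- SE = square root of the condition element of (X′V⁻¹X)⁻¹;
- bias = condition element of (X′V⁻¹X)⁻¹X′V⁻¹g, where g is the secular trend;
- type I error = Φ(−1.96 + bias/SE) + Φ(−1.96 − bias/SE).

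**Hand check.** With six even periods, a cluster crossing at period 3 has mean control period 1.5 and mean intervention period 4.5. One crossing at period 4 has 2 and 5. The gap is always 3, so a pure within-cluster contrast is biased by 3 points per 1-point trend. The random-intercept model borrows a little between clusters, which gives 2.86.

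| Layout | SE with period | SE without | Bias per 1-point trend | Type I error at trend 1 / 2 / 3 |
|---|---|---|---|---|
| Six periods, even | 8.17 | 4.93 | 2.86 | 9 / 21 / 41% |
| Seven periods, even | 8.64 | 4.79 | 3.39 | 11 / 29 / 56% |
| Six, early-sparse, largest cluster crosses first | 8.34 | 5.14 | 2.63 | 8 / 18 / 34% |
| Six, early-sparse, largest cluster crosses last | 7.96 | 4.93 | 2.44 | 8 / 17 / 32% |

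Worked entry (six even periods, 2-point trend): bias 2 × 2.86 = 5.72, which is 38% of the 15-point target. 5.72/4.93 = 1.16, and Φ(−0.80) + Φ(−3.12) is about 0.21.

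With time period in the model, a trend common to all clusters gives zero bias. A single linear period term also removes a linear trend's bias, with SE 7.92 (six even periods). Half-widths of the 95% interval are 1.96 × 8.17 = 16.0 with period and 1.96 × 4.93 = 9.7 without. Apparent power for 15 points is 0.45 and 0.86. With even recruitment and ICC 0.01 to 0.20, the SE ratio is 1.56 to 1.84.

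**AIC stage.** In simulation (N = 108, six even periods, condition and cluster already in the model), AIC left out a six-level period factor in about 89%, 84–85% and 77% of data sets at trends of 1, 2 and 3 points. It left out a linear term in 79%, 68% and 52%.

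**The case against.** The strongest reply is that this is a contingency. The planned primary model contains time period, the planned models are tried first, and the SAP gives no probability of failure. The AIC stage is more remote still and is worded as something that may be done. This stands: the fault is conditional. It does not excuse the order, because the authors wrote the rule expecting that it might be used.

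A reader might infer several stronger claims that the documents do not support:
- **That the shorter interval is wrong in itself.** With no secular trend, the interval without time period has 95% coverage. The error is bias from a trend, not the smaller standard error as such.
- **That a strong trend in outcome is documented.** The list in Recruitment rate explains slow recruitment, and the same section says COVID-19 did not affect how the trial was run for those recruited. That statement does not cover case mix or usual care, but no trend in VAS is given anywhere. The 1 to 3 points are illustrations.
- **That AIC will nearly always discard the term.** This depends on coding. The primary-outcome section describes the term as time since the trial began, which also allows a linear term, and that is kept more often.
- **That removing time period never helps fitting.** In a logistic model with sparse early periods, a period factor can cause separation. That is a reason to coarsen it, not to drop it.
- **That the unadjusted analyses share the fault.** The SAP says "Unadjusted analyses will be reported separately from these pre-specified analyses" and does not make them the test of H1.

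**Conclusion.** The point holds as a badly fixed fallback rule. If a model fails to converge, time period is the first term lost and nothing brings it back, so the reported effect becomes mainly a within-site before/after contrast. Under the assumed layouts the bias is 2.4 to 3.4 VAS points per 1-point trend per 26 weeks. A 2-point trend gives a type I error of about 17 to 29%. The standard error falls from about 8.0–8.6 to 4.8–5.1.

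These figures rest on SD 25, ICC 0.08, N = 108, assumed recruitment patterns and an assumed linear trend shared by all clusters. The true layout would change the sizes. A rising trend biased the estimate upwards in every layout tried. The documents do not show that a trend exists or that the fallback was used, so it cannot be said that the trial's result is confounded.

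**What to change.** In Effect of lower sample size on statistical analysis plan:

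1. Take time period off the removal list. State that time period and site stay in every fallback model and are forced in at the AIC step.
2. Simplify elsewhere first. Where only the 26-week value is modelled, drop the participant random effect, which cannot be separated from residual error with one value per person. Then drop prognostic covariates in a stated order.
3. If the period factor itself cannot be fitted, for example because of separation in a logistic model, merge adjacent periods or use a linear term in recruitment date. Do not remove it.
4. Label any model without calendar time as descriptive and not as a test of H1–H5.

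Returning to the full primary covariate list is not a remedy by itself, because that is the model that failed.

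The cost is a wording change to one section, best made before database lock. The price is a wider interval: in the six-period even layout, about ±16 points rather than ±10.

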### Sample size

Our sample size estimation procedure involved three steps. In the first step, we conducted a naïve sample size estimation which ignored the clustering effects of data collected through the stepped wedge design. In the second step, we calculated the design effect of the stepped wedge, using the method presented by Woertman et al. [27]. We then calculated the total sample size required by multiplying the naïve sample size calculated in the first step by the design effect and the total number of time periods in the planned design.

Our estimation was based on our primary outcome measure of Euro QOL–5D [17] VAS. We did not have any studies or preliminary data on the use of this measure in Aboriginal Australian populations. Therefore, our estimate of the effect of the intervention was based on the mean difference on the Euro QOL–5D [17] VAS between stroke and non-stroke populations in the published literature. Based on the literature [28, 29], the mean difference between stroke and non-stroke populations on the Euro QOL–5D [17] VAS was approximately 25 points with a standard deviation of 25. Guided by this information, we assumed that the intervention would result in an improvement of 15 points on the Euro QOL–5D [17] VAS (with a standard deviation 25), which equates to a standardised effect size of d = 0.6 for an independent sample t-test.

Using GPower 3.1 [30], we estimated the naïve sample size for an independent samples t-test and calculated that we would require a total of 90 participants to detect our estimated difference of d = 0.6 with 80% power at the 5% significance level.

The design effect proposed by Woertman et al. [27] is based on the number of clusters, number of steps, number of measurements at the end of each step and number of baseline measurements. Our proposed design had four clusters which were randomised to commence intervention in four steps, one baseline measurement and one measurement at the end of each step. We assumed a conservative intraclass correlation of 0.08. Based on these inputs, we calculated a design effect of 0.56. Multiplying the naïve sample size (n = 90) by the design effect (DEsw = 0.56) and the number of time periods in the trial (n = 24), and rounding-up our results to ensure that the number of patients per cluster per time period was an integer, we obtained a total sample size of 312 or 13 per cluster per time period.

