#### Caregiver strain

Data on the Modified Caregiver Strain Index [20] was obtained from 25 next-of-kin at 12 weeks post-injury and 21 next-of-kin at 26 weeks post-injury. Given the relatively small sample size for these data, differences in caregiver strain between the control and intervention phases of the trial will be assessed using independent samples *t*-tests. The *t*-tests will be conducted at the 5% significance level, and 95% confidence intervals will be reported. No additional modelling will be undertaken and no adjustments for any covariates will be made.

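### If a model fails to converge, time period is the first term removed, which would leave the stepped-wedge estimate confounded with calendar time

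*SAP article*

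**What the plan says.** As first specified, the models are sound on this point. The SAP article lists time period as a fixed effect under *Analysis principles and general considerations*, in the primary *Analysis* section, and in each secondary mixed model.

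The problem is in *Effect of lower sample size on statistical analysis plan*. That section notes that 108 participants were recruited against 312 required, and that one or more models may therefore not converge. The proposed models are tried first. If one fails, the rule is "removing effects from the model in the following order:Time periodmRS [18]Injury severityInjury typeSite". It applies to the model for any outcome, so the primary outcome is covered. If the reduced model also fails, separate 12-week and 26-week models may be built, with the remaining effects "included in the model using a forward selection strategy to achieve the best model based on the Akaike Information Criterion (AIC". No effect is stated as forced in.

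*Caregiver strain* (H5.1, H5.2) takes a different route whether or not anything converges. It uses independent-samples t-tests, and "No additional modelling will be undertaken and no adjustments for any covariates will be made".

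**The concern.** *Interim analysis* states that control comes before intervention at each site. Later recruits are therefore mostly intervention recruits, and condition is correlated with recruitment period by design. Randomising the order of crossover protects the comparison only if the model allows for time. Once period is dropped, any change over calendar time in who is recruited or how they fare is credited to, or charged against, the intervention.

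The document gives reasons to expect such change. *Recruitment rate* reports "discontinuation of approval to gain consent by proxy from 2018 to 2020", which bears on the severity of those who could be enrolled, and a pandemic from 2020 to the close of the trial. Nothing in the SAP justifies removing period first or limits how a result obtained that way may be read.

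**Working it through.** **The plan's own figure.** The inputs are "VAS (with a standard deviation 25), which equates to a standardised effect size of d = 0.6 for an independent sample t-test" and "we would require a total of 90 participants to detect our estimated difference of d = 0.6 with 80% power at the 5% significance level", with ICC 0.08. A two-sample t-test needs 44.6 per arm, hence 90. The design effect with 4 steps, one baseline and one measurement per step, and 13 per cluster-period is [1 + 0.08(52 + 13 − 1)] / [1 + 0.08(26 + 13 − 1)] × 3(0.92) / [2(4 − 1/4)] = (6.12/4.04) × 0.368 = 0.557, or 0.56. Then 90 × 0.56 × 6 = 302.4. Dividing by 24 cluster-periods gives 12.6, rounded up to 13, and 13 × 24 = 312. The figure reproduces.

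**Layout (assumed).** The figure of the implemented design is not shown. I take two control periods, then one pair crossing per period, over 6 or 7 periods, with 108 participants spread evenly.

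- Six periods: 14 control cells with mean period 34/14 = 2.43; 10 intervention cells with mean 50/10 = 5.00. The gap is 2.57 periods (about 15 months).
- Seven periods: 34/14 = 2.43 against 78/14 = 5.57. The gap is 3.14 periods (about 19 months).
- Correlation = gap × √[p(1 − p)] / SD(period), where p is the proportion in intervention. Six periods: 2.57 × 0.493 / 1.708 = 0.74. Seven periods: 3.14 × 0.5 / 2 = 0.79.

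**Bias when period is dropped.** Within a cluster that has q control periods out of T, the intervention and control mean periods are (q + 1 + T)/2 and (q + 1)/2, so they differ by T/2, that is 3.0 or 3.5. With no cluster term the difference is the raw gap, 2.57 or 3.14. A random-intercept model falls between the two. Generalised least squares on the cluster-period means (four pairs, total variance 625, ICC 0.08) gives 2.86 and 3.39 false VAS points per point of linear drift per period.

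**Standard error.** With categorical period it is 8.2 (six periods) or 8.6 (seven). Without period it is 4.9 or 4.8. Apparent power for 15 points rises from 45% or 41% to 86% or 88%.

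**Type I error** at "all outcomes will be tested independently at the two-tailed 5% significance level" is Φ(−1.96 + δ) + Φ(−1.96 − δ), with δ = bias/SE. For a drift of 1 over six periods, δ = 2.86/4.93 = 0.58, which gives 0.089.

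| Assumed drift per period (VAS) | Bias, 6 / 7 periods | Type I error, 6 / 7 periods |
|---|---|---|
| 1 | 2.9 / 3.4 | 9% / 11% |
| 2 | 5.7 / 6.8 | 21% / 29% |
| 3 | 8.6 / 10.2 | 41% / 56% |
| 5 | 14.3 / 16.9 | 83% / 94% |

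With period kept, the bias from linear drift is 0 and the error stays at 5%.

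**Uneven recruitment.** Halving recruitment in the first two periods lowers the bias per point to 2.56 (six periods) or 3.08 (seven).

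**AIC step.** In a simplified simulation (108 participants, six periods, no cluster effect, 3,000 draws per setting), AIC compared models with and without categorical period. It left period out in 90%, 85%, 78% and 51% of draws at drifts of 1, 2, 3 and 5. Type I error after selection was 8%, 17%, 29% and 40%.

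**Caregiver t-test.** There is no cluster or time term, so the raw gap applies. Each 0.1 SD of drift per period adds about 0.26 to 0.31 SD to the difference.

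**The case against.** The strongest reply is that this is a contingency. Every mixed model is first fitted with period, and the SAP says only that models may fail. A reader might infer that the planned primary analysis is confounded, or that the authors expect failure. The text supports neither, and no probability of failure can be derived from it. Nor does the AIC step exclude period: period remains a candidate, and the weakness is that it is not forced in.

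The evidence of drift also needs care. The wider recruitment window and community recruitment both came in during Period 1, when all sites were in control. A 1-point step after Period 1 would bias the effect by only about 0.3 points. The SAP says that the pandemic did not affect trial administration for recruited participants. That stands, but it does not settle who was recruited or how their quality of life changed. The drift sizes are assumed, and recruitment was uneven and lower early on. A steeper early shortfall than the one above brings the bias to about 2.3 to 2.4 per point, and the error to about 7–8%, 14–16% and 27–30% at drifts of 1, 2 and 3.

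Three further inferences are not supported:

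- That the participant random effect is the likeliest cause of failure. No fit has tested this. What can be said is that the removal list omits it, and that with one 26-week value per person it could not be separated from residual error. The general principles also list timepoint, so the intended data structure is unclear.
- That listing mRS and injury severity separately is a plain slip. The baseline tables treat them as distinct, although the primary model equates them.
- That the separate unadjusted analyses are a defect. "Unadjusted analyses will be reported separately from these pre-specified analyses" labels them as supplementary.

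Finally, categorical period does use several degrees of freedom in a small trial. That argues for a simpler time term, not for none. The caregiver t-tests are openly tied to 25 and 21 respondents. That supports a simpler analysis, but not a significance test that ignores time.

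**Conclusion.** The fallback rule is wrong as written. It removes first the term on which the stepped-wedge comparison depends, and the AIC step lets period and site stay out. If a model fails to converge, the resulting estimate, possibly the primary one, would be confounded with calendar time and would look more precise than it is.

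Under even recruitment over 6 or 7 periods the false effect is about 2.9 to 3.4 VAS points per point of drift, or about 2.5 to 3.1 with lower early recruitment. A drift of 5 points per period would mimic roughly the whole assumed 15-point benefit. These sizes rest on an assumed linear drift, an assumed layout, SD 25 and ICC 0.08. The direction of the argument does not depend on them. The proxy-consent hiatus and the pandemic period are the plausible sources of drift. The caregiver t-tests are a secondary instance that applies in every case.

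**What to change.** State that condition, time period and site stay in every fallback model, and replace the removal list with this order:

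1. Simplify or remove the participant random effect, or fit 12 and 26 weeks separately. The SAP already allows separate fits, but only as a last resort.
2. Replace categorical period with linear calendar time, which costs one degree of freedom. Use fixed site or pair effects if the site variance cannot be estimated.
3. Only then drop age, injury type or baseline mRS, in a fixed order.

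Force period and site into any model built by AIC, or delete the AIC step. For H5.1 and H5.2, report caregiver strain descriptively or adjust it for linear recruitment time. Report which step each outcome reached.

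This is a wording change, best made before database lock. The cost is a wider but honest interval: a standard error of about 8 VAS points instead of about 5. Linear time also leaves some bias if the true trend is not linear, so it should follow categorical period and not replace it from the start.

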#### Stroke disability/injury severity

The score on the mRS [18] will be dichotomised as independent (mRS [18] 0–2) or dependent /dead (mRS [18] 3–6). A mixed effects logistic regression model will be used to assess between-condition differences on this binary variable. Time period, age at recruitment, injury type and severity (dichotomised mRS [18] at baseline) will be controlled for as fixed effects in the model. Recruitment site and participant/individual will be included as random effects. In addition, time since injury and the interaction of time since injury with condition (control/intervention) will be included in the model. The interaction effect will be used to assess the between-group differences at 12 weeks post-injury [H4.1] and at 26 weeks post-injury [H4.2].

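### On non-convergence the plan deletes time period and then case-mix adjustment, never lists the participant random effect, and reaches separate 12- and 26-week models only last

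*SAP article*

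**What the plan says.** The section *Effect of lower sample size on statistical analysis plan* says the models will be tried as proposed and, if one fails, simplified by "removing effects from the model in the following order:Time periodmRS [18]Injury severityInjury typeSite". The list items have run together in the text; they are time period, mRS, injury severity, injury type and site.

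The next step is permissive: "If the model for an outcome still fails to converge, the outcome may be modelled with separate models at each timepoint". In those models "time since injury and interaction between time since injury and condition (control/intervention) will be redundant", and "The other effects will be included in the model using a forward selection strategy to achieve the best model based on the Akaike Information Criterion".

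The participant effect is neither in the removal list nor among the terms called redundant. Yet every mixed model carries it. Under *Stroke disability/injury severity* the wording is "Recruitment site and participant/individual will be included as random effects". The sections on the primary outcome, occasions of service, processes of care, functional independence, and anxiety and depression say the same.

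*Analysis principles and general considerations* states that effects on participant-level outcomes "will be adjusted for brain injury type (stroke or TBI) and severity of injury (mRS) [18] at baseline", with age, timepoint and time period as further fixed effects. *Interim analysis* notes that control comes before intervention at each site.

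**The concern.** The order gives up fixed effects that protect the comparison before it touches the random-effects structure.

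Time period goes at the first step. Each site moves one way, from control to intervention, so condition is tied to calendar time. Without period, any secular change is read partly as treatment effect. Baseline mRS and injury type, the named case-mix adjustment, go next.

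The participant effect has to be estimated from at most two values per person. In the logistic models (H3.1-H3.2 and H4.1-H4.2) those values are binary, which makes it a plausible main source of failure. A model at a single timepoint has one record per person and needs no such effect, but that option is reached only after every listed adjuster has gone. A model that converges part-way stops there and is reported in reduced form. The SAP article itself anticipates non-convergence, so the path is realistic.

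**Working it through.** **1. The shortfall that triggers the fallback.** From *Sample size*: 90 x 0.56 x 6 periods = 302.4. Over 24 cluster-periods (4 x 6) that is 12.6, rounded up to 13, and 13 x 24 = 312. Achieved: 108/312 = 34.6%, matching the plan's one-third.

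**2. What each step leaves in the model.**
- After step 1: no calendar-time control.
- After steps 2 to 4: no mRS, severity or injury type. The list counts mRS and severity as two terms, whereas the models define severity as dichotomised baseline mRS.
- After step 5: no site term; the participant effect is still present.
- Last step: one record per person. The text does not say that the participant effect goes, and the covariates return only if AIC selects them.

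**3. Is the participant effect a plausible culprit?** Two-timepoint logistic models were simulated and fitted with lme4 defaults, 20 data sets per setting. Assumed, not in the documents: eight unequal sites, six periods, 15% missing per visit, site SD 0.5, participant SD 1, 2 or 4 on the logit scale, and the covariate effects. Share of fits with convergence warnings:

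| Model | SD 1 | SD 2 | SD 4 |
|---|---|---|---|
| Full | 65% | 95% | 95% |
| Period removed | 35% | 50% | 85% |
| mRS and injury type also removed | 5% | 10% | 5% |
| Site also removed | 0% | 0% | 0% |
| Full, only the participant effect removed | 0% | 5% | 0% |

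The last row locates the source of the warnings. It is not a recommended model, because it ignores the pairing of values within a person. In that row 35-50% of fits were still singular, which reflects the site variance.

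A second simulation omitted site, used 500 trials per setting, and counted a fit as divergent when the estimated participant SD exceeded 15.
- True SD 4, 6 and 8 gave 82%, 88% and 91% agreement between the 12- and 26-week values.
- Divergence was 4%, 41% and 71% with all covariates, and 4%, 26% and 51% after period, severity and type were removed.
- Separate-timepoint logistic models with all covariates failed in at most 0.4% of trials.

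**4. What losing period could cost.** Linear check with true effect 0 and fixed site effects:

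| Assumed trend per period (VAS points) | Bias with period dropped | Share of the planned 15 points |
|---|---|---|
| 1 | +3.0 | 3.0/15 = 20% |
| 2 | +5.9 | 5.9/15 = 39% |
| 3 | +9.1 | 9.1/15 = 61% |

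The SD of the estimate fell from about 9.1-9.4 to 5.0-5.2 when period was dropped, so the biased result also looks more precise. Dropping mRS and injury type with period kept gave about zero bias when case mix was stable over time.

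**5. Is stable case mix safe to assume?** *Recruitment rate* reports that proxy consent was unavailable from 2018 to 2020. *Study design* reports a recruitment window widened from 4 to 6 weeks, and community recruitment added, during Period 1. As an assumed illustration, take a 10-20 point difference between phases in the share dependent at baseline, and a 40-point difference in later independence between dependent and independent people. The unadjusted H4 contrast then shifts by 0.10 x 0.40 = 4 to 0.20 x 0.40 = 8 percentage points.

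**6. Would AIC bring the terms back at the last step?**
- Severity and type: if they explain 10-25% of variance in a linear model, the likelihood-ratio gain is -108 ln(0.90) = 11 to -108 ln(0.75) = 31, against a penalty of 4 for two terms. They would usually return.
- Period: take six equally filled periods entered as five terms, with SD 25. A trend of s points per period has variance s^2 x 35/12. The gain is at most 108 ln(1 + s^2 x 2.917/625) = 0.5, 2.0 and 4.4 for s = 1, 2 and 3. Adding about 5 expected by chance gives 5.5, 7.0 and 9.4, against a penalty of 10. On average period would not return, even at the trends in step 4.

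**The case against.** The strongest case against runs as follows.

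- *Deleting covariates does help.* This stands. Warnings fell to 5-10% after period, mRS and injury type were removed, and divergence fell from 41% to 26% and from 71% to 51%. A reader might infer that the deletions are futile; these figures do not support that. The point is that they are probably unnecessary and give up needed terms.
- *The failure rates are assumption-driven.* This stands. The documents give no 12/26-week agreement. The high divergence rates need participant SDs of 6 to 8 logits and leave out site. A separate quadrature fit that included site found an estimated participant SD above 8 in 12% of full fits at true SD 4, and in none at 0.5 to 2. Default software warnings can be false alarms, although a false alarm could still set off the deletions.
- *AIC restores what matters.* This holds in part: severity and type would usually return, period would not, and AIC operates only at the last step.
- *The remedy is not fully tested.* This stands. The 0.4% figure comes from models without site, and singular site variance remains likely, so the fix needs a step for it.
- *Reach.* The divergence argument concerns binary secondary outcomes, which the plan calls supplementary. The removal order, however, applies to any outcome whose model fails.

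**Conclusion.** The point holds as a defect in the fallback order. As written, a model that fails and then converges part-way is reported without calendar-time control and, depending on where it stops, without the stated case-mix adjustment. A fully adjusted single-timepoint model, which needs no participant effect, is left until last.

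The size cannot be fixed from the documents. The bias of 3 to 9 VAS points needs a secular trend of 1 to 3 points per period. The shift of 4 to 8 percentage points needs case mix to differ between phases. That the participant effect is the main cause of failure is plausible and supported by simulation, but not established.

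Three stronger readings should be resisted.
- A reader might infer that case mix is the first thing lost. Time period is, and that is the more serious loss.
- A reader might put a precision cost on losing severity and type from the linear formula 1/sqrt(1 - R^2). It does not carry over to the logistic outcomes, where omitting prognostic covariates attenuates the log-odds ratio and does not widen its standard error.
- A reader might infer that the primary model must fail, because a participant intercept cannot be separated from residual error with one 26-week record each. No listed removal would cure that, but the documents do not settle whether only 26-week data enter: the primary-outcome section names no timepoint term, while *Analysis principles and general considerations* includes one.

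**What to change.** Rewrite the fallback in *Effect of lower sample size on statistical analysis plan*:

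1. On failure, first fit separate 12- and 26-week models without a participant effect, keeping condition, time period, age, injury type, baseline mRS and the site term. State explicitly that the participant effect is dropped here.
2. If the site variance is singular, simplify the site term next.
3. Only then remove non-design covariates in a fixed order, or use a penalised logistic fit for binary outcomes. Keep time period throughout.
4. Delete the AIC forward selection.
5. List baseline mRS and injury severity as one term, or say how they differ.

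This changes wording only. The cost is small: in this fallback a person missing at 26 weeks no longer contributes through the 12-week value. Keeping period also forgoes the smaller standard error of a model without it, but that gain comes from assuming no secular trend.
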